### 7.3.1. Reporting Procedures for Serious Adverse Events

The Data Monitoring Committee (DMC) will review all SAEs for the study at certain time-points of the trial. The DMC is detailed in Appendix B and may hold personal /TC/electronic meetings. The DMC will meet at regular intervals and consider:

- Occurrence and nature of adverse events
- Whether additional information on adverse events is required
- Consider taking appropriate action where necessary to halt the trial (see below)
- Act / advise on incidents occurring between meetings that require rapid assessment (e.g. SUSARs)

Especially before the second and third trial cohort, when the Day 30 results for each patient are available, the DMC must meet and make a go/no-go decision for the treatment of the next dose cohort, which needs to be reported to the PI as soon as possible.

All SAEs will be reported to the DMC within one day of discovery or notification of the event. All SAE information will be recorded on an SAE form, which will be sent electronically to members of the DMC. Additional information received for a case (follow-up or corrections to the original case) will be detailed on a new SAE form.

The CRO will – on behalf of the Sponsor - report all AEs, SAEs and SUSARs to the Ethics Committee and the Regulatory Authority (PEI) in an annual safety report. Fatal or life-threatening SUSARs will be reported within 7 days and all other SUSARs within 15 days. The PI will also inform all members of the study group on all adverse events that might affect the safety of participants.

### 7.4. Rules for discontinuation of the trial

Any of the following events will result in discontinuation of the trial:

5. Severe loss of vision (more than 15 letters ETDRS acuity) occurring deemed to be a result of vector administration.
6. Severe ocular, vector-induced inflammation, unresponsive to treatment (endophthalmitis).
7. Any suspected unexpected serious adverse reaction (SUSAR).
8. Safety concerns other than those mentioned under 1-3 and consecutive request for discontinuation by the Data Monitoring Committee.

If an Adverse Event was the reason for discontinuation of the trial either by the PI or the participant, the participant must undergo an early termination visit (see flowchart). The patient must be given appropriate care under medical supervision until symptoms cease or the condition becomes stable. Maximal follow-up duration will be 1 year after trial termination

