## **3. Study Plan**

### **3.1. Study Design**

This is an open mono-center trial with fellow-eye comparison. Three patients will be assigned to three consecutive, increasing dosage groups (see figure 3):

4) low dose:  $\leq 1 \times 10^{10}$  vgp (n=3)

Between each injection (between patient 1 and 2 and patient 2 and 3) a safety interval of 4 weeks will be kept.

After collection of data on study visit Day 30 of all three patients of the dose cohort and before the scheduled start of the next injections of the consecutive dosage group the DMC will meet and evaluate safety data. If no safety concerns are reported the next dosage group of patients will be treated as scheduled. DMC advice may also result in a dose reduction for the next dosage cohort.

5) intermediate dose:  $\leq 5 \times 10^{10}$  vgp (n=3)

Between each injection (between patient 4 and 5 and patient 5 and 6) a safety interval of 4 weeks will be kept.

After collection of data on study visit Day 30 and before the scheduled start of the next injections of the consecutive dosage group the DMC will meet and evaluate safety data of groups 1 and 2. If no safety concerns are reported the next dosage group of patients will be treated as scheduled. DMC advice may also result in a dose reduction for the next dosage cohort. Within the high dose cohort, the interval between injections / individual patients will be four weeks.

6) high dose:  $\leq 1 \times 10^{11}$  vgp (n=3)

Between each injection (between patient 7 and 8 and patient 8 and 9) a safety interval of 4 weeks will be kept.

The following figure (Fig. 3) explains the schedule and timelines of dose groups and the points of decisions of the data monitoring committee.

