### 7.2. Safety

#### 7.2.1. Ocular and systemic safety

**Safety** as primary endpoint will be assessed by clinical examination of  
*Ocular safety*

3. loss of  $\geq 15$  letters visual acuity at 1m
4. severe, vector-induced, intraocular inflammation unresponsive to treatment

*Systemic safety*

5. vital signs
6. routine clinical chemistry testing (including CRP, IgG, IgM and full/differential blood counts)
7. Immunopathology essays will include specific enzyme-linked immunosorbent assays for humoral antibodies against rAAV8 capsid protein
8. Biodistribution will be monitored by polymerase chain reaction studies on rAAV2/8 genome in blood, urine, saliva and lachrymal fluid.

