#### *(3) Immune reactions and/or toxic effects on retinal function caused by AAV8-CNGA3*

Due to the time required for transgene expression following subretinal delivery of AAV8, it is unlikely that any toxic effects of the transgene product would be evident prior to at least two weeks after surgery at the earliest. These might include similar immune reactions as described in (2) above. Also any toxic effects of AAV8-CNGA3 on visual function might be manifest by a worsening of visual acuity after the initial period of post-operative recovery. Potential toxic effects on retinal function are likely to be manifest as a significant drop in visual acuity (defined by 15 letters or more).

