| cataract formation                           | 1-5%                                               | 9%                     | 10-20%                               |
| transient intraocular hypertension           | 5%                                                 | 0%                     | 5%                                   |
| corneal erosion                              | 5-20 %                                             | 5-20 %                 | 5-20 %                               |

**Table 2:** Risks of complications during 23g PPV referring to literature, previous NHP studies and expected rates for the planned trial. [1] Wilkinson et al., 2013 [2] Lee et al., 2012 [3] Wykoff et al., 2010.

Regarding 2) there is a risk for a loss of vision due to ophthalmic immune reactions to the vector (indirect) or due to direct effects of the vector (however, pre-clinical

[figure not shown]

studies showed no toxic effects with up to 10 fold higher concentrations). If any immune reaction should be triggered by the vector, this might include non-infectious inflammation of the pigment epithelium (epitheliitis), retina (retinitis), vitreous cavity (vitritis) or uveal tissue (uveitis). None of these have been reported in any previous clinical trial involving AAV in ocular gene transfer.

Such effects may result in a significant deterioration of visual function (decrease in VA of  $\geq 15$  letters) and might also occur after initial improvement. A vulnerable period for direct and/or indirect (immunogenic) effects due to the viral packaging protein of the vector would be the first two weeks (time of concomitant steroid treatment). No clinical trial has as of yet reported immune-reaction to the transgene (even in systemic gene transfer). It therefore seems unlikely that a direct or indirect effect due to transgene expression would occur after ocular gene transfer in the immune-privileged subretinal space.

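### Stopping rule 1 in section 7.4 starts one letter above the 15-letter loss used everywhere else, so a vector-attributed loss of exactly 15 letters does not trigger the automatic stop

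*Supplement*

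**What the plan says.** All references are to protocol version 5.0, the latest in the Supplement. Four places set a cut-off for loss of visual acuity.

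- Section 7.4, rule 1, is one of the events that oblige the trial to stop: "Severe loss of vision (more than 15 letters ETDRS acuity) occurring deemed to be a result of vector administration". The list is printed as items 5 to 8, but the last item refers back to items 1 to 3, so I call them rules 1 to 4.
- Section 7.2.1 gives the first ocular component of the primary safety endpoint: "loss of $\geq 15$ letters visual acuity at 1m".
- Section 7.2.3, item (3), on immune or toxic effects of the expressed transgene, says that toxicity would probably show as a "significant drop in visual acuity (defined by 15 letters or more").
- Section 7.5, on the effects of the vector, speaks of a "significant deterioration of visual function (decrease in VA of $\geq 15$ letters").

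Section 7.4 also has a rule for any SUSAR (rule 3) and a residual rule (rule 4): "Safety concerns other than those mentioned under 1-3 and consecutive request for discontinuation by the Data Monitoring Committee".

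**The concern.** Rule 1 is clear when read alone: a loss of 15 letters does not meet it, and a loss of 16 does. The difficulty appears when it is read beside the other three sections. The rule that compels action has a stricter cut-off than the endpoint it guards and than the protocol's own description of vector toxicity. The protocol does not explain why.

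The trial is a first use in humans with nine patients, three per dose, and its primary aim is safety. Each event will be weighed individually. The plan chose to make a vector-related loss of vision an automatic reason to stop. At exactly 15 letters that automatic step is lost, although the loss counts as a primary safety event. What happens next becomes a matter of judgement.

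**Working it through.** The protocol gives no figure to reproduce here. Section 10.2 states that no sample size calculation was made, and this point rests on none. The check sets the four cut-offs side by side.

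Let L be the loss in whole letters. I assume that all four sections refer to the same ETDRS letter score and the same reference reading.

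| Section | Role | Condition on L | Vector attribution required |
|---|---|---|---|
| 7.2.1 | primary ocular safety endpoint | L ≥ 15 | no |
| 7.2.3, item (3) | significant toxic drop | L ≥ 15 | toxicity is the subject of the item |
| 7.5 | significant deterioration from vector effects | L ≥ 15 | vector effects are the subject of the paragraph |
| 7.4, rule 1 | automatic stop | L > 15, that is L ≥ 16 | yes |

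Now take a loss that has been judged to result from the vector, so that attribution is satisfied, and vary L.

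- L = 14: not a primary event, and rule 1 is not met. The sections agree.
- L = 15: a primary event under 7.2.1, a significant drop under 7.2.3 and a significant deterioration under 7.5. Since 15 > 15 is false, rule 1 is not met. The sections disagree.
- L = 16 or more: a primary event, and rule 1 is met. The sections agree.

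The set of losses covered by the endpoint but not by rule 1 is {15, 16, 17, …} minus {16, 17, …} = {15}, a single value.

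At L = 15, two routes to a stop remain in 7.4.

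- Rule 3 applies if the event is classed as a SUSAR. Section 7.2.3 ties that to the Investigator's Brochure, which is not among the documents, so this route can be neither relied on nor ruled out.
- Rule 4 applies if the DMC asks for discontinuation. That is a decision of the committee and does not follow automatically from the event.

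If rule 1 read L ≥ 15, the conditions on L would be the same in all four sections, and no other value of L would change status.

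**The case against.** The best case for the present wording is that an endpoint and a stopping rule do different work. The endpoint records any loss of 15 letters or more, whatever its cause. Rule 1 ends the trial, asks for a severe loss and requires attribution to the vector. Sections 7.2.3 and 7.5 call 15 letters significant, not severe. A stopping rule may properly be narrower than its endpoint. This stands for the attribution condition, which may well be deliberate and should stay. It does not explain the cut-off: a single letter is not a credible step from significant to severe, and nothing in the text presents it as one.

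It is also fair to say that the practical effect is small. The DMC meets regularly (7.2.2), receives every serious adverse event within one day, can act between meetings, and must give a go/no-go before the second and third cohorts (7.3.1). All of this stands and sets the severity.

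Three stronger readings are tempting but not supported.

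- A reader might infer that rule 1 is a lone slip because rule 2 copies its endpoint. The endpoint is "severe, vector-induced, intraocular inflammation unresponsive to treatment" and the rule is "Severe ocular, vector-induced inflammation, unresponsive to treatment (endophthalmitis"). The bracketed term is absent from the endpoint and could narrow rule 2 as well, so the comparison proves little.
- A reader might infer that within a cohort only the waiting time protects the next patient: "Between each injection (between patient 1 and 2 and patient 2 and 3) a safety interval of 4 weeks will be kept". The DMC provisions above apply there too. Section 3.1 also refers to Figure 3 for the committee's decision points, and that figure is not shown.
- A reader might infer that a 15-letter drop can never be a SUSAR because 7.2.3 describes it under its heading on expected events. The SUSAR definition refers expectedness to the Investigator's Brochure, so the heading does not settle the matter.

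**Conclusion.** The mismatch is real and appears on the face of the current protocol. A vector-attributed loss of exactly 15 letters is a primary safety event and meets the protocol's definition of significant toxicity, but falls outside the rule that would stop the trial automatically.

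The severity is minor. One whole-letter value is affected, and only when the loss is judged to be due to the vector. The remaining question is whether a stop follows by rule or by a further decision. I make no claim about how often such a loss would occur, since the documents give no basis for one. The analysis in section 10.4 is descriptive, and no planned estimate depends on the stopping threshold. The conclusion rests on the assumption stated above about a common letter score and reference reading. It does not say that the trial lacks safety oversight or that such an event would go unnoticed.

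**What to change.** In section 7.4, rule 1 (printed as item 5), replace the present cut-off with a loss of 15 letters or more, and leave the requirement that the loss be deemed a result of the vector as it is. The rule then uses the same cut-off as 7.2.1, 7.2.3 and 7.5. If the sponsor does intend a higher bar for stopping, the alternative is to say so in 7.4 and give the reason.

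The change needs no new data, visits or analyses. As with any change to the protocol, it would go to the authority and the ethics committee as an amendment under section 13. The one downside is that a vector-attributed loss of exactly 15 letters would now end the trial without room for discretion.

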### Adverse Reaction (AR)

An AR or adverse reaction is an untoward and unintended reaction to a medicinal product related to any dose. The phrase "reaction to a medicinal product" means that a causal relationship between a study medication and an AE is at least a reasonable possibility, i.e., the relationship cannot be ruled out. All cases judged by either the reporting medically qualified professional or the sponsor as having a reasonable suspected causal relationship to the study medication qualify as adverse reactions.

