### Serious Adverse Reaction (SAR)

A SAR, a serious adverse reaction, is an adverse event (expected or unexpected) that is both serious and, in the opinion of the reporting investigator, believed with reasonable probability to be due to one of the study treatments, based on the information provided.

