### 7.3. Reporting Procedures for all Adverse Events

All AEs occurring during the study observed by the investigator or reported by the participant, whether or not attributed to study medication, will be recorded on the CRF. The following information will be recorded: description, date of onset and end date, severity, assessment of relatedness to study medication, action taken and the outcome of AEs.

AEs considered related to the study medication as judged by a medically qualified investigator or the sponsor will be followed until resolution or the event is considered stable and/or until the end of the follow-up period (4 years).

The severity of events will be assessed on the following scale: 1 = mild, 2 = moderate, 3 = severe. The relationship of AEs to the study medication will be assessed by a medically qualified investigator and discussed with the PI.

[figure not shown]

Any *pregnancy* occurring during the clinical study and the outcome of the pregnancy of female patients or fathered by trial participants, should be recorded and followed up for congenital abnormality or birth defect until delivery. Pregnancy itself is documented as AE, in case of hospitalization as SAE.

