### 14. Ethical and Regulatory Aspects

The Investigator will be responsible for the overall conduct of the clinical trial and will be responsible for ensuring the trial is conducted according to the protocol and all regulatory requirements and regulations.

The protocol and informed consent form for this study must be approved by an appropriately constituted EC as defined by local requirements. The list of the EC voting members, their titles or occupation, and their institutional affiliations and/or the EC general assurance number, if applicable, must be provided with the approval. The EC will also be notified of completion of the study and a final report must be submitted to the EC and the PEI in accordance with local requirements. The Investigator will maintain an accurate and complete record of all communications, reports and submissions to the PEI and EC.

This trial is subject to German AMG in its current version and will be submitted, performed and monitored according to ICH-GCP standards. Any study procedure will only be performed after the patient has given written informed consent. Informed consent will be documented in the electronic patient file of the Centre for Ophthalmology (AIS) giving the date of consent, study name and the name of the physician. Each subject's signed informed consent must be kept on file by the Investigator.

German data protection regulations will be followed and patients will be informed in a standardized and detailed manner about pseudonymized health data and about those persons/institutions who will have access to personal data under special restrictions according to law.

The Sponsor of this trial is UKT (Universitätsklinikum Tübingen) represented by the Principal Investigator. Defined tasks have been delegated to the CRO of the trial, STZ *eyetrial* at the Centre for Ophthalmology, University of Tübingen such as, but not limited to, communication with regulatory authorities, submission of the trial to PEI and EC, monitoring of the trial, safety reports. UKT has contracted insurance for trial participation as well as travel insurance.

The contact information for **patient insurance** are:

[REDACTED]

Contact information for **travel insurance** are:

[REDACTED]

The amount covered for the patient insurance is 500 000€ per patient. The amount covered for the travel insurance is 100 000€ for invalidity und 50 000€ in the case of death.

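### A loss of more than 15 letters judged non-serious and not vector-related need not reach the DMC before the next patient in the same cohort is injected

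*Supplement*

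**What the plan says.** All references are to protocol version 5.0.

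- **Stopping rule (7.4).** The trial is discontinued for "Severe loss of vision (more than 15 letters ETDRS acuity) occurring deemed to be a result of vector administration". A loss put down to something other than vector administration does not trigger this rule. The fourth rule lets the DMC request discontinuation, but only for concerns other than those in the first three.
- **Endpoint (7.2.1).** A loss of 15 letters or more is the first ocular item of the primary safety endpoint. It carries no causality condition; the second item, inflammation, does.
- **Reporting to the DMC (7.3.1).** "All SAEs will be reported to the DMC within one day of discovery or notification of the event". No time limit is given for non-serious events. The DMC considers adverse events at regular meetings, with no interval stated, and may advise on urgent incidents in between.
- **Serious events (7.2.3).** The criteria are death, threat to life, hospitalisation, disability and congenital anomaly. No criterion refers to letters lost or to a threat to sight.
- **Escalation (3.1, 7.3.1).** The DMC must give a go/no-go before the second and third cohorts, after the Day 30 data. Within a cohort, the only stated condition for the next injection is a four-week interval.
- **Causality (7.3).** "The relationship of AEs to the study medication will be assessed by a medically qualified investigator and discussed with the PI".

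**The concern.** This is a nine-patient, first-in-human escalation, and the stopping and review rules exist mainly to protect the next patient. Vitrectomy, a deliberate detachment that includes the fovea, and the vector are all given in one session (6.1). When acuity then falls sharply, the cause may be hard to assign. If the investigator ascribes the fall to surgery and does not class it as serious, the stopping rule is not triggered and the one-day report is not due. Between cohorts the DMC would still see the event before the dose rises. Within a cohort, nothing in the text shown ensures that the independent committee knows of it before the next injection at the same dose. What is at stake is timely notice: the event would still be recorded and would still count towards the safety endpoint.

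**Working it through.** The plan gives no figure on this point to reproduce. The check traces the route of such an event and compares the visit windows with the four-week interval.

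**1. Route of a loss of more than 15 letters in the treated eye**

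| Judgement | Stopping rule 1 | One-day report to the DMC |
|---|---|---|
| Vector-related, serious | applies | yes |
| Vector-related, non-serious | applies | not required by 7.3.1, but the trial stops |
| Not vector-related, serious | does not apply | yes |
| Not vector-related, non-serious | does not apply | no |

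Only the last row leaves both routes silent. A loss of exactly 15 letters meets the endpoint but not the stopping threshold, so for it the DMC route depends on seriousness alone.

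**2. Steps affected**

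- Next-patient steps: 9 − 1 = 8.
- Steps preceded by a mandatory DMC decision: 2 (patient 3 to 4, and 6 to 7).
- Within-cohort steps: 3 cohorts × 2 = 6 (1–2, 2–3, 4–5, 5–6, 7–8, 8–9), and 2 + 6 = 8.

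**3. What is measured inside the interval**

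- Interval: 4 weeks = 28 days.
- ETDRS acuity at D14 ± 3 = days 11–17, always inside.
- ETDRS acuity at D30 ± 5 = days 25–35. Of these 11 days, 4 (25–28) fall inside and 7 (29–35) after.
- One ETDRS test is therefore certain to precede an injection on day 28. Section 8.4.11 suggests that acuity is taken before each slit-lamp examination, but neither the flowchart nor 8.2 schedules best corrected acuity on D1 to D3.
- Slit-lamp and fundus examinations after the injection day: D1, D2, D3 and D14, so 4. Inflammation is watched more closely than acuity.

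**4. Time available for a DMC reply**

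- From a D14 finding to day 28: 28 − 17 = 11 to 28 − 11 = 17 days.
- After a one-day report: 11 − 1 = 10 to 17 − 1 = 16 days.

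This takes the next injection on day 28. A later injection would leave more time. The documents give no rate for losses of this size or for doubtful attribution, so no probability is computed.

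**The case against.** The case against is substantial.

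- **Two judgements must coincide.** Retinal detachment, traumatic cataract, haemorrhage and endophthalmitis are listed among expected serious events in 7.2.3, and a drop of 15 letters or more is named there too. Prolonged hospitalisation or significant disability also makes an event serious. Many large losses would reach the DMC in one day whatever their cause. What remains is mainly transient loss after a planned foveal detachment. This stands, and it makes the gap narrow.
- **Vector administration may include the surgery.** Section 7.5 counts the surgical procedure among the risks of the vector injection. On that reading, a surgical loss of more than 15 letters stops the trial and the gap closes. But 7.5 goes on to separate surgical from vector effects, and 10.2 distinguishes vector-related from procedure-related events. The wording stays open.
- **Other channels exist.** The DMC can act between meetings, and 7.3.1 has the PI tell the study group about adverse events that bear on participants' safety. The DMC can act only on what it is told, however, and the text does not say that it belongs to the study group.
- **Figure 3 and Appendix B are not shown.** Both concern the DMC, and either may contain a within-cohort check.

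A reader might infer more: that the protocol has no causality assessor or standard for its stops. The documents do not support that. Section 7.3 names the assessor for all adverse events, and 7.2.3 defines an adverse reaction as one where a causal link "is at least a reasonable possibility, i.e., the relationship cannot be ruled out". The serious-reaction definition is worded differently ("in the opinion of the reporting investigator, believed with reasonable probability to be due to one of the study treatments"), and 7.4 points to neither, but that is at most a missing cross-reference. Nor should the adverse-reaction standard be tied to the automatic stops. With surgery and vector given together, a transient day-14 loss could then end the trial.

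**Conclusion.** The point holds in a limited form. In the version 5.0 text shown, a loss of more than 15 letters that is judged non-serious and not attributed to the vector need not reach the DMC before the next injection in the same cohort. This concerns 6 of 8 next-patient steps. That count describes where the gap could open and says nothing about how often it would.

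A reader might also infer that such a loss would escape the DMC altogether. It should not: it goes on the case report form, and the DMC considers adverse events at its meetings and decides before each dose increase. The weakness is late notice. It bears on acuity far more than on inflammation, since severe inflammation that resists treatment would almost always be a serious event.

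The conclusion rests on three assumptions: that vector administration in 7.4 does not cover the delivery surgery, that Figure 3 and Appendix B add no within-cohort review, and that injections remained to be given. On the last, section 3.2 planned the last patient's first visit for November 2016, before version 5.0 (16 February 2017), and the documents do not say whether dosing was complete. If it was, the change matters only for replacement patients or later studies. This is a cheap improvement worth considering; it is not a fault that undermines the trial.

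**What to change.** - **In 7.3.1:** report every loss of 15 letters or more in the treated eye to the DMC within one day, whatever its presumed cause or seriousness, on the form and by the electronic route already used for serious events. Hold the next injection in the same cohort until the DMC has replied.
- **In 7.4:** state that the fourth rule lets the DMC request discontinuation for such a loss, even though acuity loss is mentioned in the first rule.
- **Leave unchanged:** the letter threshold for stopping, and the investigator's role in attributing cause.
- **If Figure 3 or Appendix B already provides this:** a cross-reference is enough.

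The cost is a short amendment and a few ad hoc consultations with a DMC that may already confer by telephone or electronically. Some reports will concern day-14 losses that resolve as the retina recovers, and an injection may occasionally be held briefly. The 10 to 16 days left after a one-day report of a D14 finding should usually absorb this. A loss first seen at D30 may come too late to hold an injection given on day 28.
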